## Abstract

**Background:**

Comprehensive assessment of integrated care deployment constitutes a major challenge to ensure quality, sustainability and transferability of both healthcare policies and services in the transition toward a coordinated service delivery scenario. To this end, the manuscript articulates four different protocols aiming at assessing large-scale implementation of integrated care, which are being developed within the umbrella of the regional project Nextcare (2016–2019), undertaken to foster innovation in technologically-supported services for chronic multimorbid patients in Catalonia (ES) (7.5 M inhabitants).

Whereas one of the assessment protocols is designed to evaluate population-based deployment of care coordination at regional level during the period 2011–2017, the other three are service-based protocols addressing: i) Home hospitalization; ii) Prehabilitation for major surgery; and, iii) Community-based interventions for frail elderly chronic patients. All three services have demonstrated efficacy and potential for health value generation. They reflect different implementation maturity levels. While full coverage of the entire urban health district of *Barcelona-Esquerra* (520 k inhabitants) is the main aim of home hospitalization, demonstration of sustainability at Hospital Clinic of Barcelona constitutes the core goal of the prehabilitation service. Likewise, full coverage of integrated care services addressed to frail chronic patients is aimed at the city of Badalona (216 k inhabitants).

**Methods:**

The population-based analysis, as well as the three service-based protocols, follow observational and experimental study designs using a non-randomized intervention group *(integrated care)* compared with a control group *(usual care)* with a propensity score matching method. Evaluation of cost-effectiveness of the interventions using a Quadruple aim approach is a central outcome in all protocols. Moreover, multi-criteria decision analysis is explored as an innovative method for health delivery assessment. The following additional dimensions will also be addressed: i) Determinants of sustainability and scalability of the services; ii) Assessment of the technological support; iii) Enhanced health risk assessment; and, iv) Factors modulating service transferability.

**Discussion:**

The current study offers a unique opportunity to undertake a comprehensive assessment of integrated care fostering deployment of services at regional level. The study outcomes will contribute refining service workflows, improving health risk assessment and generating recommendations for service selection.

**Trials registration:**

NCT03130283 (date released 04/06/2018), NCT03768050 (date released 12/05/2018), NCT03767387 (date released 12/05/2018).

**Electronic supplementary material:**

The online version of this article (10.1186/s12913-019-4174-2) contains supplementary material, which is available to authorized users.

## Background

Core elements of integrated care (IC) are connectivity, alignment and collaboration within and between the cure and care sectors. The goal is to enhance quality of care and quality of life, consumer satisfaction and system efficiency for patients suffering from chronic disorders, that need multiple services, providers and settings in different levels of care [1–3]. Useful approaches [4] have identified two main systemic levels (i.e. horizontal and vertical) at which integration of health and social care sectors can occur. Horizontal integration links community-based services while vertical integration brings together specialized and primary care under one functional (or structural) management umbrella through shared care agreements framed into well-defined service workflows.

Since early 2000’s, large scale implementation of IC is being strongly promoted by relevant international agencies and governments [5, 6] because of its high potential to effectively address the healthcare and societal challenges generated by population ageing and unhealthy lifestyles. However, several aspects implicit in the transition towards real care coordination scenarios, must be taken into account and properly solved to ensure adoption. First, since IC services are applied to complex patients and in evolving settings, the need for flexible standardization of the interventions, as well as changes in the roles of patients and health professionals is a must. Second, the coordination between several stakeholders and/or healthcare tiers often requires profound organizational adaptations which, in turn, involve the need for novel business models and reimbursement incentives to drive management change. Last but not least, quickly evolving digital technologies are facilitating coordination and personalization of care, as well as complex data management, but extensive adoption of digital health supporting IC needs to be accelerated.

All of the above factors contribute to explain the difficulties encountered in the process of standardization of IC assessment. Over the past several years, evaluation of well-established IC programs, alongside pilot experiences, has been undertaken in several countries with mixed results [7–9]. Overall, these experiences have contributed to the generation of a series of general recommendations on evaluation of IC with focus on service transferability across geographical sites aimed at fostering regional scalability [4, 10]. It is of note, however, that application of these recommendations for a comprehensive assessment of deployment of IC services in real-life scenarios is clearly an unmet need.

The current manuscript aims to describe a structured evaluation framework (Fig. 1) that articulates four comprehensive assessment protocols covering both vertical and horizontal levels of integration. One assessment protocol reports a population-based assessment of outcomes from past and current Catalan Health Plans, 2011–2015 [11] and 2016–2020 [12], respectively, whereas the other three assessment protocols address the deployment of specific IC services during the period 2017–2018, namely: i) Home hospitalization [13]; ii) Prehabilitation of candidates for major surgery [14]; and, iii) Community-based advanced care service for frail elderly [15, 16]. The ultimate aim of the research is to explore the application of innovative evaluation strategies [4] for IC services deployed in real-life settings. To this end, a comprehensive evaluation of outcomes following a Quadruple Aim approach [17, 18], deployment strategies and maturity of implementation will be performed within each of the four assessment protocols of the study.

**Fig. 1 Fig1:**
[figure not shown]
The figure depicts the main elements of the structured evaluation framework that articulates the four assessment protocols described in the current report. The proposed comprehensive assessment of integrated care services includes their impact at population level. A core component of the assessment protocols includes the identification of Key Performance Indicators (KPI) useful for long-term follow-up of health services after adoption encompassing three dimensions: health outcomes, processes and structure

The Catalan Health Care System dispenses services for 7.5 inhabitants, providing universal coverage through a tax-based system. Administratively, it is composed by a single public payer and multiple service providers publicly or privately owned. Since 2006, the implementation of IC services in one of the four healthcare sectors in the city of Barcelona (520 k inhabitants) was instituted by the Hospital Clinic of Barcelona (HCB), a tertiary university hospital [19], adopting the Chronic Care Model as the conceptual reference [20, 21]. Moreover, the subsequent Health Plans for Catalonia after 2011, have addressed the deployment challenges by giving priority to new modalities of healthcare delivery for chronic patient care including empowerment of patients and carers. To date, clear examples of clinical effectiveness have been produced for the three IC services presented in this report: Home hospitalization [13, 22, 23], prehabilitation [14] and community-based services for frail patients [9]. It is expected that lessons learned from the implementation of the four protocols reported in the current manuscript will foster regional scalability and sustainability of IC services in Catalonia. Moreover, it is also expected that the recommendations generated by these deployments in real-life settings will significantly contribute to facilitate transferability and comparability of IC services at international level. The context in which these four assessment protocols will take place is described in [11] and [19].

## Methods

The four protocols (Table 1) follow observational and experimental non-randomized study designs. In all cases, comparability between the intervention group and the control group will be achieved using a propensity score matching (PSM) [24, 25] method, as described in detail below. The common methodology for assessing health-value generation of the interventions in each protocol will follow a Quadruple Aim approach [17, 18] considering pre-defined variables for: i) Health and well-being; ii) Experience with care; iii) Operational costs; and, iv) Health professionals’ engagement, as summarized in the second column of Table 2. It is of note that the outcomes of the three first dimensions (Triple Aim approach) [26, 27, 30] will be assessed both separately and jointly. The later will consist of a multi-criteria decision analysis (MCDA) recently developed [31, 32] and currently applied in 17 selected IC programs from 8 European countries [33]. The MCDA approach broadens the scope of the evaluation taking into account patient health reported outcomes and stakeholders’ views on those same outcomes allowing standardized comparisons between seemingly dissimilar IC programmes. Moreover, engagement of health professionals, the fourth pillar of the Quadruple Aim approach, will be assessed using the questionnaires currently applied in [34], aiming at assessing main drivers of large-scale deployment of IC services in 5 European regions.

**Table 1 Tab1:** Main characteristics of the four assessment protocols

Protocol	Aims	Study design & Measurements	Intervention group	Comparator group	Expected outputs
(1) Population-based study	(1.1) Impact of integrated care on cost-effectiveness	(1.1) Case control study matching registry data using PSM methods (2011–2017) (Additional file 1: Table S1)	(1.1 and 1.2) Residents living in the healthcare district of Barcelona-Esquerra (*n* = 516 K inhabitants)	(1.1 and 1.2) Residents living in the other 3 healthcare districts of Barcelona (~ 400 k inhabitants each), as well as the entire region of Catalonia (*n* = 7.5 M inhabitants)	(1.1a) Health value generation of integrated care
	(1.2) Enhanced health risk assessment and service selection	(1.2) Fixed cohort study			(1.1b) Enhanced Key Performance Indicators (KPI) for long-term assessment of integrated care
					(1.2) Proposal for health risk assessment for service selection
(2) Home hospitalization	(2.1) Assessment of hospital avoidance and early hospital discharge at district level	(2.1) Prospective controlled cohort study using PSM methods (2017–2018) (Additional file 2: Table S2)	(2.1) All patients admitted to the home hospitalization directly from the emergency room (*n* = 800 patients). Study of a deeply characterized subset (triple aim approach) of 200 patients. This subset will be used to generate (2.2).	(2.1) Patients admitted to conventional hospitalization directly from the emergency department of the same hospital (n = 800 patients). Study of a deeply characterized subset (triple aim approach) of 200 patients. This subset will be used to generate (2.2).	(2.1a) Health value generation of the service; expanded HDA using MCDA (n = 200). Factors modulating success of the implementation strategy.
		(2.2) Observational mixed-methods study combining network and cluster analyses with qualitative methodologies			
	(2.2) Recommendations for shared-care agreements between specialized and community-based care				
					(2.1b) KPI for service assessment
					(2.2) Strategies for enhanced interactions between specialized-community-based care.
(3) Prehabilitation	(3.1) Sustainability (cost-effectiveness of prehabilitation at HCB	(3.1) Prospective controlled cohort study using PSM methods (2016–2018) (Additional file 3: Table S3)	(3.1) All candidates for major surgery at HCB receiving prehabilitation (*n* = 500)	(3.1) Candidates for major surgery at HCB receiving usual care in the same hospital (*n* = 250)	(3.1a) Health value generation of prehabilitation at HCB
	(3.2) Recommendations for transition toward a regional peri-operative care program	(3.2) Randomized controlled trial to assess peri-operative care	(3.2) Candidates for major surgery at HCB receiving peri-operative care (*n* = 60)		(3.1b) KPI for service assessment
	(3.3) Enhanced pre-operative risk assessment	(3.3) Fixed cohort study	(3.3) All surgical patients in the last 5 years at HCB	(3.2) Candidates for major surgery at HCB receiving usual care (n = 60)	
					(3.2) Cost-effectiveness of peri-operative care and strategies for regional deployment.
					(3.3) Risk assessment tool for personalized prehabilitation
(4) Frail elderly patients	(4.1) Assessment of community-based integrated care services for frail patients at BSA	(4.1) Prospective controlled cohort study using PSM methods (2018) (Additional file 4: Table S4)	(4.1) Individuals enrolled in BSA integrated care programs for frail elderly that includes: i) Early Discharge support (*n* = 144); ii) Long-term home-based support services (*n* = 566) and iii) Geriatric residences care (*n* = 920)	(4.1) Individuals living in Badalona receiving usual care: i) After hospital discharge (n = 144), ii) At home (n = 566); and, iii) Living at geriatric residences (*n* = 920)	(4.1a) Cost-effectiveness of the service; and, expanded HDA using MCDA (n = 250). Factors modulating success of the implementation strategy.
					(4.1b) KPI for service assessment

**Abbreviations**: *HDA* Health Delivery Assessment, *MCDA* Multi-Criteria Decision Analysis, *HCB* Hospital Clinic de Barcelona, *PSM* Propensity Score Matching, *KPI* Key Performance Indicators for service long-term assessment after the deployment phase, *BSA* Badalona Serveis Asssistencials

**Table 2 Tab2:** Three main assessment dimensions: effects of the intervention, determinants of success of implementation and maturity of integration

Study Protocol	Outcomes of the intervention [26, 27]		Deployment strategies [28, 29]	Maturity level [4]
(1) Population-based	Mortality, general practitioner visits, community-nurse visits, cumulative days per year admitted in hospital, emergency department visits, all hospital admissions, potentially avoidable hospitalizations, multiple drug prescription, needs for social support, costs per patient per year (Additional file 1: Table S1)		A. What are the possible factors and agents responsible for good implementation of a health intervention? B. What are the possible factors for enhancing or expanding a given health intervention? C. What describes the context in which implementation occurs? D. What describes the main factors influencing implementation in a given context? To be assessed using a mixed methods approach: combining qualitative and quantitative methods	Assessment of the twelve dimensions of the Maturity Model for Integrated Care, both at health system and health services levels, promoted by the European Innovation Partnership for Active and Healthy Ageing, following the instructions reported in reference (4). These twelve dimensions are: 1. Readiness to Change 2. Structure & Governance 3. Information & eHealth Services 4.Standardization& Simplification 5. Finance & Funding 6. Removal of Inhibitors 7. Population Approach 8. Citizen Empowerment 9. Evaluation Methods 10. Breadth of Ambition 11. Innovation Management 12. Capacity Building
(2) Home hospitalization	Health and well-being	Mortality rate 30/90 days after discharge, place of death, avoidable hospital admissions, total bed days, 12 months before admission (hospital and community resources); 30-day after discharge (hospital and community resources), transitional care strategies (palliative care, primary care or hospital care)		
	Patient experience	Person centeredness, continuity of care (Additional file 2: Table S2)		
	Costs	Operational costs		
(3) Prehabilitation	Health and well-being	Cumulative hospital days of stay, intensive care unit length of stay, number of complications per patient, costs from the perspective of the hospital including inpatient services, diagnostic procedures, pharmaceutical consumption and blood products consumption, aerobic capacity, physical activity, psychological status, health status (Additional file 3: Table S3)		
	Costs	Operational costs		
(4) Frail elderly	Health and well-being	Mortality rate, avoidable hospital admissions, total bed days, 30-day readmissions, number of ER visits in the month, physical functioning, psychological well-being, social relationships & participation, enjoyment of life, resilience, autonomy		
	Patient experience	Person centeredness, continuity of care, burden of medication, burden of informal caregiving (Additional file 4: Table S4)		
	Costs	Operational costs		

The current assessment protocols also aim to separately establish key factors that modulate the success of IC service deployments in order to identify their potential for transferability to other sites. To this end, we will use standard implementation science tools [28, 29, 35, 36] to answer the questions delineated in the third column of Table 2, as well as to report the results of the implementation process following standards for reporting implementation studies (StaRI) [28]. This will allow us to identify facilitators, barriers, solutions and critical success factors during the course of the implementation process with relevant implications for analysis of service transferability. It must be highlighted that collaborative tools and methodologies were applied for the implementation of the three service-oriented studies. The process incorporates co-design elements, with participation of different stakeholders, including patients, following a Plan-Do-Study-Act (PDSA) iterative cycles approach [37] adapted to the characteristics of each assessment protocol, as summarized below. Last, but not least, the maturity of the ecosystem in which the service is being deployed will be assessed following the twelve-dimension measurement protocol described in [4] and summarized in the fourth column of Table 2.

It is assumed that the three assessment categories depicted in Fig. 1 and in Table 2: i) Outcomes, ii) Deployment strategies, and, iii) Maturity level, will provide the basis for identification of general, and service-specific, key performance indicators (KPI) useful for long-term follow-up of IC services after the initial deployment period, taking into account outcomes, processes and structure [38].

The assessment protocols will combine three different data sources. First, registry data obtained from the Catalan Health Surveillance System (CHSS) [16, 39, 40], as briefly described below. Second, individual data extracted from the electronic healthcare records from primary care and specialized care. Third, data derived from prospectively applied standardized questionnaires to patients, health professionals and managers (Additional file 1: Table S1, Additional file 2: Table S2, Additional file 3: Table S3 and Additional file 4: Table S4). The challenges involved in the combination of different datasets used in these four assessment protocols have been overcome within the framework of the recent EU General Data Protection Regulation (GDPR) [41].

The CHSS includes updated registries from primary care, hospital-related events (e.g. hospitalization, emergency room and specialized outpatient visits), pharmacy, mental health, socio-sanitary services, respiratory therapies, dialysis, outpatient rehabilitation and non-urgent transport of all citizens living in Catalonia (7.5 M) since 2011. The information is updated every 6 months. It provides a basis for cost analyses of the use of healthcare resources, pharmacy consumption, and prevalence of key health problems. The CHSS feeds the regional population-based risk stratification tool named Adjusted Morbidity Groups (GMA) that complies with the following characteristics: i) A population health approach; ii) No licensing constraints; iii) Open source computational algorithms; and, iv) The adjusted morbidity grouper relies mostly on statistical criteria, as opposed to other tools that include expert-based coefficients, thus facilitating quick transferability to other territories [39, 42].

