#### Assessment protocol 3: Prehabilitation service

This is a preventive intervention targeted at high risk candidates for major surgical procedures carried out preoperatively aiming at reducing complications and enhancing postoperative recovery. It combines: i) Motivational interviewing; ii) High-intensity endurance exercise training; iii) Promotion of physical activity; iv) Nutritional supplementation; and; v) Psychological support.

The intervention is currently deployed as a mainstream service at HCB in several types of major surgeries. During fall 2017, three multidisciplinary workshops using a design-thinking approach were carried out to refine the service workflow and to explore the potential for service scalability. The outcomes of the co-design process provided a robust background for the design of a future personalized perioperative care service at regional level covering three phases: prehabilitation, in-patient care, and post-discharge rehabilitation.

The current assessment protocol aims to assess cost-effectiveness of prehabilitation as a mainstream service in the ongoing deployment at HCB, as well as to generate a roadmap for regional scalability of the service. It is planned as a prospective controlled cohort study including 500 consecutive patients undertaking prehabilitation, as the intervention group, and patients following standard care before surgery, in the same hospital (i.e. HCB), as the control group (2:1 intervention to control ratio). The patients will be included from the following type of surgeries: major digestive surgery (*n* = 525), lung volume reduction (*n* = 30), radical cystectomy (*n* = 30), major cardiovascular surgery (*n* = 165). Study groups will be made comparable using PSM with the following matching variables: type of surgery, age, sex, American Society of Anaesthesiologists index and GMA grading. Patients’ clinical outcomes will be assessed at baseline, pre-surgery and 30 days after surgery. The primary outcome will be cost-effectiveness, meaning reduced hospital stay and early re-admissions. Secondary outcome variables will include number of complications per patient, healthcare use, aerobic capacity, physical activity and psychological and health status. The specificities of the assessment protocol are summarized in Additional file 3: Table S3.

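### Protocol 3 defines its arms by prehabilitation received and does not match on pre-operative time or baseline function, so candidates who declined, could not train or were operated on early can serve as controls and confound the comparison

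*Protocol article*

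**What the plan says.** Both arms of aim 3.1 are described by care actually had. In Table 1 (row 3) the intervention arm is "3.1) All candidates for major surgery at HCB receiving prehabilitation" (n = 500) and the comparator is "3.1) Candidates for major surgery at HCB receiving usual care in the same hospital" (n = 250). The section on assessment protocol 3 repeats this as "500 consecutive patients undertaking prehabilitation, as the intervention group, and patients following standard care before surgery, in the same hospital", with a "2:1 intervention to control ratio".

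The same section describes the service in two ways that bear on who is left to be a control:
- It is established at the hospital: "The intervention is currently deployed as a mainstream service at HCB in several types of major surgeries".
- It is selective: "This is a preventive intervention targeted at high risk candidates for major surgical procedures".

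Comparability rests on propensity score matching on "type of surgery, age, sex, American Society of Anaesthesiologists index and GMA grading". The primary outcome is cost-effectiveness, understood as shorter stay and fewer early re-admissions. Clinical outcomes are measured at baseline, before the operation and 30 days after it. Aerobic capacity, physical activity and psychological status are among the secondary outcomes.

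**The concern.** Where a service is routine, a candidate can go without it for reasons that are themselves prognostic: refusal, inability to do the training, or an operation scheduled too soon. Each such patient meets the written definition of a control. Taking the intervention patients consecutively does not help, because the series is consecutive only among those who took the service up.

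The programme includes endurance training and motivational work, so uptake plausibly depends on motivation, physical ability and available time. None of the five matching variables measures these directly. ASA and GMA grade illness burden. They do not record how long a patient waited or how fit the patient was at indication.

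The primary comparison could then partly reflect differences between people who can and will prepare for surgery and people who cannot or will not. A larger sample would not remove this. The text also does not say which arm holds a patient who starts the programme and stops.

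**Working it through.** **1. The plan's own counts.** The surgery types are listed as "major digestive surgery (*n* = 525), lung volume reduction (*n* = 30), radical cystectomy (*n* = 30), major cardiovascular surgery (*n* = 165"): 525 + 30 + 30 + 165 = 750. The arms give 500 + 250 = 750 and 500/250 = 2. The counts agree. The article gives no alpha, power, effect size or SD for this comparison, so there is no power calculation to reproduce.

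**2. Who can be a control.** The passages leave at least three routes into the control arm:
- The candidate was offered prehabilitation and declined, or could not train. Outcome plausibly worse.
- The candidate was operated on too soon to take part. Outcome plausibly worse, if early surgery marks urgency.
- The candidate was not targeted because the risk was lower. Outcome plausibly better.

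Surgery type is a matching variable. Matched controls should therefore come mostly from surgery types in which prehabilitation was delivered, and its absence in other types does not close the first two routes.

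**3. Size in days.** All inputs here are assumptions; none is in the article. Let f be the share of controls who declined or had no pre-operative time, and x their excess stay that remains after matching, whatever the effect of prehabilitation.

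Spurious difference = f × x:
- 0.10 × 1 day = 0.1 day
- 0.25 × 2 days = 0.5 day
- 0.50 × 3 days = 1.5 days

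With an assumed SD of 10 days, SE = 10 × √(1/500 + 1/250) = 10 × √0.006 = 0.77 day. The three cases are about 0.13, 0.65 and 1.9 standard errors.

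**4. Chance of a misleading significant result.** Assume no true effect, a two-sided 5% test, and an outcome shift of d SD in the share f. The bias is f × d and the standard error is √0.006 = 0.0775 SD. Without bias, the chance of a significant result favouring prehabilitation would be 2.5%.

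| f | d (SD) | Bias (SD) | Chance of a significant result favouring prehabilitation |
|---|---|---|---|
| 0.10 | 0.2 | 0.02 | 4% |
| 0.25 | 0.3 | 0.075 | 16% |
| 0.50 | 0.3 | 0.15 | 49% |
| 0.50 | 0.5 | 0.25 | 90% |

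For scale, the difference detectable with 80% power is (1.96 + 0.84) × 0.0775 = 0.217 SD.

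**5. Opposing selection.** Now add a share g of lower-risk, non-targeted controls whose outcome is better by e SD. Net bias = f × d − g × e:
- 0.3 × 0.3 − 0.3 × 0.3 = 0
- 0.5 × 0.3 − 0.2 × 0.5 = +0.05 SD
- 0.2 × 0.3 − 0.5 × 0.3 = −0.09 SD, against prehabilitation

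The sign depends on the make-up of the control arm, which the article does not give.

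**The case against.** The strongest case on the other side has four parts.

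- **Direction.** A reader might infer that the design makes prehabilitation look better. The documents do not support that. They do not say why controls went without the service, and they do say that it is aimed at high-risk candidates. Lower-risk controls would bias the other way, and matching on ASA and GMA removes part of any difference in either direction. This part stands. Possible cancellation between two unmeasured selections is still no protection.
- **Details held elsewhere.** Specifics of this protocol are referred to Additional file 3 (Table S3), which is not shown and may contain eligibility rules for controls. This stands as a limit on confidence. The matching list, however, is given outright in the article, and it lacks pre-operative time and baseline function.
- **Schedule.** A baseline and a pre-surgery assessment, not restricted to one arm, suggest that controls had some interval before surgery. That makes controls with no pre-operative time less likely, but it sets no minimum interval. It also suggests that baseline function is already being collected and could be used.
- **Target of estimation.** A reader might also infer that evaluating a mainstream service must mean estimating the effect of offering it. That is one reasonable reading. An effect among those treated is a legitimate target for a matched cohort, and the article does not settle the choice. Rebuilding the study around never-offered controls could itself bring in lower-risk, non-targeted patients.

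**Conclusion.** The point holds as a flaw in how the arms and the matching are fixed. It does not hold as a demonstrated bias in one direction. Followed as written, the plan admits as controls candidates who declined, could not train or were operated on too soon, and no matching variable captures pre-operative time or baseline functional capacity. Stay and re-admissions can be biased, plausibly towards prehabilitation, with offset or reversal possible.

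The size is unknown. The range of 0.1 to 1.5 days assumes that 10–50% of controls are of this kind and that an excess stay of 1–3 days survives matching. Its middle value, 0.5 day, is smaller than one standard error, and the standard error itself rests on an assumed SD of 10 days. It would go too far to say that the controls do consist of refusers and urgent cases; the text shows only that such patients qualify. Confidence is medium because Table S3 could narrow the control definition. The change is worth making because it is cheap.

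**What to change.** 1. Restrict controls to candidates who, at surgical indication, met the service's own eligibility criteria and had enough time before the operation to undertake it.
2. Keep everyone who starts prehabilitation in the intervention arm, whether or not they complete it.
3. Record for each control why prehabilitation was not received (declined, unable, no time, not offered).
4. Add to the propensity model the interval from indication to operation (or urgency), and baseline aerobic capacity, physical activity and psychological status where measured in both arms.
5. As sensitivity analyses, report results excluding decliners, or with arms formed by documented offer.

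If Table S3 already contains item 1 or 2, it is enough to state it in the main text.

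**Cost.** The work is mainly in extracting referral and waiting-list dates and in coding the reasons. Fewer controls will qualify, and keeping partial users in the intervention arm dilutes the effect somewhat. Prehabilitation may itself lengthen the wait, so the interval is best taken from the operation date planned at indication rather than the date on which surgery took place.
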